### Clinical Significance

Supplementary analyses will consider the clinical significance of any effect (ie, meaningful changes in the participant’s life) [156]. Effect sizes will be calculated for all primary and secondary outcomes. These group-level examinations of effectiveness will also be supplemented by metrics of individual-level change for all primary and secondary outcomes. A reliable change index will be used to assess changes beyond those attributable to chance or measurement error [157]. Clinically significant change, as outlined by Jacobson and Truax [156], will subsequently be calculated using functional score ranges where possible (Gambling Symptom Assessment Scale score of ≤20) or a convention of at least a 25% change in scores in the positive direction [158]. At the posttreatment and 6-month follow-up evaluations, each participant’s status will be defined as *recovered* (final score falls into the functional range and corresponds to a reliable change), *improved* (final score falls into the dysfunctional range and corresponds to a reliable change), *unchanged* (final score does not correspond to a reliable change), or *deteriorated* (final score corresponds to a relative change in the negative direction).

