### Within-Group Follow-up Evaluation

A within-group evaluation of outcomes over a 6-month follow-up period will supplement the MRT to (1) evaluate within-group change over a longer period and (2) explore predictors of longer-term treatment outcomes (including app use over the 6-month follow-up period). Although the preintervention survey will be automated via the app before beginning the 28-day MRT period, participants will be prompted by email to complete the postintervention and follow-up surveys via Qualtrics (Qualtrics XM). Descriptive and covariate measures will include participant type (gambler, family member or friend, and clinician, researcher, or policy maker), sociodemographic characteristics, problem gambling activities, intended gambling behavior (measured using the Timeline Follow-Forward, a novel adaptation of the Timeline Follow-Back [148]), and other help-seeking (measured using the Help Seeking Questionnaire [149]). The primary outcome will be gambling symptom severity (measured using the Gambling Symptom Assessment Scale [129]), and secondary outcomes will include gambling frequency and expenditure (measured using a timeline follow-back at the preintervention evaluation, the EMA event record data at the posttreatment evaluation, and single items at the 6-month evaluation) and the cognitive processes targeted by the intervention: craving severity (measured using the Penn Gambling Craving Scale [25]), self-efficacy (measured using the Brief Situational Confidence Questionnaire-Gambling [130]), and positive outcome expectancies (measured using the Excitement, Escape, and Money subscales of the Gambling Outcome Expectancies Scale [69]; Multimedia Appendix 4). Each evaluation will be completed in approximately 10 to 15 minutes. Ideally, follow-up evaluation surveys will also be conducted 12 and 24 months after the intervention, but this will be dependent on obtaining additional funding.

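### Applied as written to gambling frequency and expenditure, the reliable change index would class many participants who stop gambling as unchanged, and probably most of them if expenditure is heavily skewed

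*Protocol article*

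**What the plan says.** The Clinical Significance section of the protocol article supplements the group-level results with "metrics of individual-level change for all primary and secondary outcomes. A reliable change index will be used". It then defines four statuses at the posttreatment and 6-month evaluations. *Recovered* means that the "final score falls into the functional range and corresponds to a reliable change". *Improved* also requires reliable change, with the final score still in the dysfunctional range. *Unchanged* is defined only by the lack of it: "final score does not correspond to a reliable change".

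The one functional range given is a "Gambling Symptom Assessment Scale score of ≤20". Where no range exists, the section offers "or a convention of at least a 25% change in scores in the positive direction".

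The Within-Group Follow-up Evaluation section brings the behavioural measures into scope: "secondary outcomes will include gambling frequency and expenditure (measured using a timeline follow-back at the preintervention evaluation", then "the EMA event record data at the posttreatment evaluation, and single items at the 6-month evaluation". Neither section states a transformation, an exception or a separate rule for these two outcomes.

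**The concern.** A reliable change index asks whether a change exceeds what measurement error would produce, and it applies the same absolute cut-off to everyone. That suits a multi-item scale with roughly constant error and a known reliability. Expenditure and frequency are different. They are bounded at zero, and the recruitment criteria admit gamblers of any symptom severity, so a wide spread is plausible. The heaviest gamblers then drive the SD, and the cut-off can exceed a lighter gambler's whole baseline.

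Such a participant cannot register improvement by any reduction, including quitting. On expenditure, where increases have no ceiling, the only statuses open to them are *unchanged* and *deteriorated*. The intervention is aimed at people who want to quit or gamble less, and the Discussion presents the follow-up as a way to consider clinical impact. Reporting quitters as unchanged would understate that impact on both behavioural outcomes.

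A separate difficulty is that an index of measurement error needs a reliability for the instrument, and here the instrument differs at each of the three time points. No single reliability fits.

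**Working it through.** **Inputs.** The article states no SD, CV, skew, reliability or threshold for these outcomes, so there is no figure to reproduce. The 1.96 criterion, the reliabilities and the distributions below are all assumptions.

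**Step 1: threshold.** A change is reliable if |x₂ − x₁| > 1.96 × SD × √(2(1 − r)). With a complete stop x₂ = 0, so the status is *unchanged* whenever the baseline x₁ < k × SD, with k = 1.96√(2(1 − r)). This gives k = 1.52 at r = 0.7, 1.24 at r = 0.8 and 0.88 at r = 0.9. This step needs no distributional assumption.

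**Step 2: expenditure, log-normal baseline.** In units of the mean, the threshold is t = k × CV, σ² = ln(1 + CV²), and the share below the threshold is Φ[(ln t + σ²/2)/σ].

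For CV 1 and r 0.8: t = 1.24, σ² = 0.693, σ = 0.833, and (0.215 + 0.347)/0.833 = 0.675, so the share is 75%.

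| CV | r = 0.7 | r = 0.8 | r = 0.9 |
|---|---|---|---|
| 0.6 | 54% | 40% | 19% |
| 0.7 | 66% | 54% | 32% |
| 1 | 82% | 75% | 60% |
| 1.5 | 90% | 87% | 79% |
| 2 | 93% | 91% | 86% |
| 3 | 96% | 95% | 92% |

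Over CV 0.7 to 3 the range is 32% to 96%. A gamma baseline gives similar values (CV 1: 78%, 71%, 58%).

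In money terms, a mean spend of 1000 with CV 1.5 and r 0.8 gives a threshold of 1859. The median spend is 1000/√(1 + 1.5²) = 555, so a median spender who quits is *unchanged*.

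**Step 3: a check that does not use the log-normal.** The threshold exceeds the mean baseline once CV > 1/k, which is 0.66, 0.81 and 1.14 at r = 0.7, 0.8 and 0.9. If the median lies below the mean, as is usual under right skew, more than half the sample is then below the threshold.

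**Step 4: frequency as days out of 28**, beta-binomial, among those with at least one gambling day.

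| Mean (SD) days | r = 0.7 | r = 0.8 | r = 0.9 |
|---|---|---|---|
| 6.6 (5.9) | 74% | 66% | 56% |
| 7.4 (5.0) | 57% | 50% | 34% |
| 11.3 (5.8) | 35% | 29% | 18% |
| 16.8 (5.8) | 9% | 7% | 3% |
| 16.8 (4.0) | 1% | <1% | <1% |

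**Step 5: the alternatives.** Under the 25% convention a complete stop is a 100% reduction, so no quitter with a non-zero baseline is missed. An index on log(1 + x) misses 0% to 3% of quitters on expenditure (assumed mean 1000, CV 0.6 to 3). On frequency with a mean of about 7 days and r = 0.8, its cut-off is about 1.1 to 1.3 days, so one-day gamblers who stop (about 6% to 11%) are still missed.

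**The case against.** The strongest reply is that the defect depends on a choice the article does not state. It does not say that the index is computed on raw dollars or days, and a fuller plan could transform the data. That limits the finding to the rule as published, which promises individual metrics for all outcomes and gives these two no exception.

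The text also leaves room for a milder reading. The promise covering all outcomes and the naming of the index are in separate sentences. The statuses refer to a functional range, and only the symptom scale has one. One could therefore read the statuses as applying to that scale, with the 25% convention serving the rest. However, the convention is offered as a substitute for a missing functional range, to be applied after the index, and the definitions of *recovered* and *improved* still require reliable change. At best the wording is ambiguous, and the same sentence would resolve it.

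Two stronger readings are tempting. A reader might infer that most quitters would be misclassified on both outcomes. The documents do not support that, because spread and reliability are not given. For expenditure the share falls below half at CV 0.6 with r of 0.8 or more, and for frequency it is below half in many scenarios. A reader might also infer that the index cannot be computed because event records and single items have no internal consistency. That does not follow, since test-retest reliability could be used. The real obstacle is the change of instrument.

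**Conclusion.** The point holds in limited form. As published, the rule applies a reliable change index to two zero-bounded outcomes, and on the raw scale anyone with a baseline below 1.96 × SD × √(2(1 − r)) cannot be credited with improvement, even for quitting. That much is algebra. How many people this affects is an assumption: many for expenditure, and probably most if it is heavily skewed, but anywhere from almost none to somewhat over half for frequency in days at r = 0.8. The changing instrument is a separate limitation of any change score on these outcomes.

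The section labels these analyses supplementary. The primary proximal analysis and the GEE analyses of long-term outcomes do not use the index and are unaffected. This is an inexpensive improvement worth making before the individual-level results are reported.

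**What to change.** Limit the reliable-change statuses to the multi-item scales: symptom severity, craving, self-efficacy and positive outcome expectancies. For frequency and expenditure, report the proportion with at least a 25% reduction from their own non-zero baseline, and the proportion with no gambling at each evaluation. Participants with a zero baseline would be counted separately.

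An index on log(1 + x) is second best. It still misses some low-baseline quitters, and for expenditure the result depends on the currency unit.

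The cost is one sentence of analysis wording and no new data. The small downside is that the behavioural outcomes would use a different individual-change metric from the scales. The fix does not remove the effect of changing instruments, so the report should state that individual change in these two outcomes may partly reflect the method of measurement.

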### Participant Recruitment and Reimbursement

Participants will be recruited across Australia and New Zealand, using a range of strategies, such as web-based advertising (eg, Google Adwords), social media (eg, Facebook and Instagram), gambling-related websites (eg, GambleAware, Gambling Helpline, Gambling Help Online, and Australasian Gaming Council), and advertisements in public places (eg, universities, general practices, health services, mental health services, and alcohol and other drug services). Gambling counseling services and gambling venues may also be requested to assist with participant recruitment. The eligibility criteria will include (1) current Australian or New Zealand residence, (2) ≥18 years of age, (3) installation of the app from an internet-enabled smartphone, (4) willingness to receive notifications from the app, (5) fluency in the English language, and (6) seeking support for one’s own gambling. The target population for *GamblingLess: In-The-Moment* comprises people who want to quit or gamble less. Consistent with a pragmatic design, the intervention will be available to any interested gambler, regardless of the level of gambling symptom severity or whether they are seeking other forms of support or treatment [124]. Moreover, consistent with a harm minimization approach, participants can select abstinence or nonabstinence treatment goals [125-127]. Participants in the trial will be compensated for their time in e-gift vouchers: US $0.70 for each EMA completed and a US $14 bonus if >75% of the EMAs are completed (to a maximum of US $70), US $35 for completion of the postintervention survey, US $50 for completion of the 6-month follow-up survey, and US $35 for the optional semistructured interview.

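### The recovered category sets no baseline condition in a trial open to any symptom severity, and the four status labels overlap as printed

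*Protocol article*

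**What the plan says.** The Clinical Significance section first introduces the change criterion: "A reliable change index will be used to assess changes beyond those attributable to chance or measurement error". Clinically significant change is then judged "using functional score ranges where possible (Gambling Symptom Assessment Scale score of ≤20"), or, where no such range exists, by "a convention of at least a 25% change in scores in the positive direction".

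Each participant is given one of four statuses at the posttreatment and 6-month evaluations:

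- A participant counts as *recovered* if the "final score falls into the functional range and corresponds to a reliable change".
- The second status, *improved*, is given when the "final score falls into the dysfunctional range and corresponds to a reliable change".
- The third, *unchanged*, has no range condition and applies whenever there is no reliable change.
- The last, *deteriorated*, is worded differently from the others: "final score corresponds to a relative change in the negative direction".

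Participant Recruitment and Reimbursement opens the app to any interested gambler "regardless of the level of gambling symptom severity". Statistical Analyses names clinically significant change in symptom severity as an example outcome for the models of longer-term predictors. The Clinical Significance section describes its analyses as supplementary.

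**The concern.** Recovery on a functional cut-off means crossing it from the dysfunctional side. The printed definition looks only at where the participant ends. In a trial with a severity threshold at entry this would do no harm, because everyone would start on the dysfunctional side. This trial has no such threshold, and the Research Questions section also offers the app as a relapse prevention tool during recovery, so low starting scores are to be expected.

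The printed labels are also not mutually exclusive. Two of them state no direction of change, one drops the word reliable, and no order of precedence is given.

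The follow-up evaluation has no control arm, so the proportions recovered and improved will be read at face value. The Introduction reports the pilot in that form (10/21, 48%, recovered or improved). The same classification may serve as the outcome in the predictor models.

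**Working it through.** The document states no figure that depends on this rule, so there is nothing to reproduce. The check has three parts.

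**1. Applying the printed definitions to score pairs.** The cut-off of 20 is the protocol's. The reliable-change threshold is assumed to be 9 points (derived in part 2); a threshold of 10 gives the same labels.

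| Baseline → final | Labels met as printed |
|---|---|
| 30 → 15 | recovered |
| 38 → 26 | improved |
| 30 → 28 | unchanged |
| 18 → 5 | recovered, though never above 20 |
| 30 → 31 | unchanged and deteriorated |
| 24 → 40 | improved and deteriorated |
| 4 → 18 | recovered and deteriorated |

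The first three rows behave as intended. The fourth is wrong however kindly the text is read. The last three depend on literal reading.

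**2. Size of the baseline problem.** The document gives no baseline mean, SD, reliability or amount of change. All of the following are assumptions: integer scores on 0 to 48, SD 9, reliability .87, mean true improvement 5 points, SD of true change 7, with independent measurement error at each occasion.

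Reliable-change threshold = 1.96 × SD × √(2(1 − r)) = 1.96 × 9 × √0.26 = 8.99, that is, 9 points.

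Simulating 2 million paired scores under the printed rule:

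| Assumed baseline mean | Starting at ≤20 | Recovered as printed | of which started ≤20 | of which started >20 |
|---|---|---|---|---|
| 30 | 15% | 21% | 4 points | 17 points |
| 26 | 27% | 26% | 7 points | 19 points |
| 22 | 43% | 29% | 12 points | 17 points |

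The fourth column includes the few who reached a final score of 20 or less by a reliable rise. Counting reliable decreases only, the figures are 3.6, 6.9 and 11.0 points.

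As shares of everyone labelled recovered, these are 4/21 = 19%, 7/26 = 27% and 12/29 = 41%. At a baseline mean of 26 with a true-change SD of 4.5 instead of 7, the figure is 6 of 21 points. Over a wider grid (baseline mean 20 to 30, SD 8 to 10, reliability .80 to .90, mean improvement 0.5 to 1.0 SD), about 10% to 50% of those labelled recovered improved from a start at 20 or less. The spread follows the assumed proportion starting there (12% to 53%).

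**3. Size of the overlap under literal coding.** With no true change and continuous scores, P(change > 0) = 50% and P(change > 1.96 × S_diff) = 2.5%. Of 200 participants, 0.50 × 200 = 100 would be labelled deteriorated, against 0.025 × 200 = 5 under a reliable-change rule. With integer scores and the part 2 assumptions (baseline mean 26), the figures are 45% and 3%. All of that 45% carry a second label: 42 points are also unchanged, and 3 points are also recovered or improved.

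**The case against.** The strongest reply is that most of this is wording. Three of the four categories say reliable, and the paragraph introduces a reliable change index precisely to exclude measurement error. Relative is therefore most plausibly a slip, and an analyst would not label a one-point rise as deterioration. The names recovered and improved imply a direction, worsening has a category of its own, and the section follows a cited method. This largely stands for the overlap.

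A reader might infer from part 3 that the trial will report about 45% deteriorated where 3% is right. The document does not support that, because the contrast arises only if the slip is coded literally. Nor can one say that the whole rule lacks direction: deteriorated has one, and so does the 25% convention.

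The reply does not reach the missing baseline condition. Replacing relative with reliable and adding a direction would still leave the 18 → 5 participant recovered. It can fairly be said that entry requires seeking support for one's own gambling, so few may start at 20 or less, and that the document gives no figure for this. That limits what can be claimed about size. It is also not an omission of the kind an article leaves to a fuller document, because the article prints a complete status rule and applies it to each participant.

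**Conclusion.** The point holds, at moderate severity. Because entry is open to any severity and recovered has no baseline condition, the rule counts as recovered some participants who were never in the dysfunctional range. The number cannot be derived from the document; the illustration of 4 of 21 to 12 of 29 percentage points rests wholly on the assumed mean, SD, reliability and change.

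The overlap of labels is real as printed but probably unintended, and it matters only if the text is coded as it stands. It would go too far to conclude that participants will be misclassified throughout, or that harm will be inflated.

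The reach is limited to the supplementary responder proportions and the exploratory predictor models. The primary microrandomized comparison and the analysis of the symptom severity score over time do not use these categories.

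**What to change.** Restate the rule for the Gambling Symptom Assessment Scale as follows:

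- *recovered*: baseline above 20, reliable decrease, final score 20 or less
- *improved*: baseline above 20, reliable decrease, final score above 20
- *unchanged*: no reliable change
- *deteriorated*: reliable increase

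Report participants who start at 20 or less separately, by reliable change only, and give their number. Use the same definitions wherever clinically significant change is an outcome in the predictor models. Settle this before any outcome data are classified.

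The cost is a change of wording, with no new data and no change of design. The one real downside is a smaller denominator for recovered and improved, and so less precise proportions.

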### Sample Size

The project aims to recruit a sample of 200 participants. A sample size of 120 participants would provide >80% power to detect a small true intervention effect size for the primary binary outcome (ie, gambling episode) of relative risk=1.21 (at Cronbach α=.05; availability parameter=0.3; randomization *P*=.25; outcome without intervention *P*=.25) [159,160]. In *GamblingLess: Curb Your Urge*, attrition was 39% when considering participants who completed the baseline measures and 19% when considering participants who downloaded the app after completing the baseline measures [116]. As such, this project will provide sufficient power to detect true effects even under a conservative attrition rate of 40% from the original sample of 200 participants at baseline.

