A microrandomized trial (MRT), a form of sequential factorial design in which every participant serves as their own control, will be used to inform the optimization of this JITAI [93,98]. In this MRT, each participant will be randomized to a tailored intervention condition or no intervention control condition at each decision point across a 28-day period [121,122]. The primary aim of the MRT is to explore whether it is worthwhile to deliver a tailored intervention option at a time of cognitive vulnerability. Specifically, the aim is to explore whether, compared with the delivery of no intervention, the delivery of a tailored intervention reduces the probability of a subsequent gambling episode (primary proximal outcome) and improves craving intensity, self-efficacy, and positive outcome expectancies (secondary proximal outcomes). It is hypothesized that the delivery of a tailored intervention will be more effective than no intervention in reducing the probability of a gambling episode and improving craving intensity, self-efficacy, and positive outcome expectancies by the subsequent EMA. Should data allow, secondary exploratory research questions include the following:

*Which type of intervention option is most beneficial at a time of cognitive vulnerability?* Is the delivery of one intervention option (targeting cravings, self-efficacy, or positive outcome expectancies) more likely to reduce the probability of a subsequent gambling episode than the other intervention options?*Under what conditions is the delivery of an intervention option most beneficial?* How do time-variant (EMA) factors (time of day, time of week, craving intensity, self-efficacy, positive outcome expectancies, psychological distress, impulsivity, subjective alcohol intoxication, readiness to change, gambling availability [financial and location], and social context) and time-invariant (preintervention survey) factors (gambling symptom severity, gambling frequency, gambling expenditure, gender, and age) influence the intervention effect on the probability of a subsequent gambling episode?*How do the proximal effects of intervention options change over time as the treatment progresses?* How does the effect of a tailored intervention on the probability of a subsequent gambling episode change over the course of the 28-day MRT?

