### Microrandomization Protocol

The microrandomization procedure will then be applied, whereby eligible participants will be microrandomized to a tailored intervention condition or no intervention control condition (Figure 1). Overall, the microrandomization procedure will involve eligible participants having a 75% chance of being microrandomized in the tailored intervention condition and a 25% chance of being microrandomized in the no intervention control condition. However, because the reformulated relapse prevention model does not presume that certain factors are more influential than others [15], participants exceeding the cut point on more than one of these tailoring variables will be randomly allocated to a relevant intervention option (curbing cravings, tackling triggers, or exploring expectancies). Specifically, participants who are eligible for 2 intervention options will have a 37.5% chance of receiving either intervention option, and those who are eligible for 3 intervention options will have a 25% chance of receiving any of the intervention options. This microrandomization protocol is fully automated, which guarantees that the administration of treatments and assessment of outcomes are blinded.

Following completion of each EMA, participants who are microrandomized to the no intervention control condition will be sent an encouraging message, and their interaction with the app will end. Participants microrandomized to the tailored intervention condition will be sent to the relevant intervention dashboard, which comprises a menu of intervention activities from which they can select. Specifically, participants who are allocated to the craving intervention will be taken to the craving intervention dashboard and asked to select an intervention activity. In contrast, participants who are allocated to the self-efficacy and expectancies interventions will be asked to select a specific type of trigger or expectation, administered an EMA item specific to their selected trigger or expectation (Multimedia Appendix 3), then taken to the relevant intervention dashboard, and asked to select an intervention activity.

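### The inputs printed for the >80% power claim contradict the 75/25 design and the expected fall in gambling; under the design, power at 120 participants is 71% or 87% depending on an effect size the protocol does not state

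*Protocol article*

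**What the plan says.** Sample Size (protocol article): "A sample size of 120 participants would provide >80% power to detect a small true intervention effect size". The inputs printed for this claim, which concerns the primary proximal outcome, are "relative risk=1.21 (at Cronbach α=.05; availability parameter=0.3; randomization *P*=.25; outcome without intervention *P*=.25". The section does not name the condition to which the randomization probability or the relative risk refers, and it does not say whether the test is one- or two-sided. It then concludes that power is sufficient even if 40% of 200 participants are lost, which leaves 120.

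Microrandomization Protocol: "eligible participants having a 75% chance of being microrandomized in the tailored intervention condition", with the remaining 25% going to control.

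Research Questions: the hypothesis is that "the delivery of a tailored intervention will be more effective than no intervention in reducing the probability of a gambling episode". The Abstract and the Distal and Proximal Outcomes section give the same direction.

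Decision Points: three EMAs a day for 28 days, so 3 × 28 = 84 decision points per participant.

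**The concern.** Two printed inputs do not describe this trial. A randomization probability of .25 is the design's chance of control, not of treatment. A relative risk of 1.21 on a no-intervention rate of .25 means that the intervention raises gambling to .25 × 1.21 = .3025, the opposite of the hypothesis.

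Neither is a harmless change of label. The variance of a log relative risk depends on which arm holds more observations and on which arm has the rarer outcome, so swapping arms or inverting the ratio changes the power. The conclusion about 40% attrition rests on exactly the 120-participant figure. If that figure is wrong, a null primary result could be read as stronger evidence of no effect than it is. If the intended effect was larger, the protocol misdescribes what the trial can detect.

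**Working it through.** **Inputs.** n = 120, availability 0.3, RR 1.21, no-intervention rate .25 and α = .05 (Sample Size); T = 84 (Decision Points); treatment probability π = .75 (Microrandomization Protocol). Assumed here: a two-sided test, constant effect and availability, and every next EMA completed.

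**Available decision points.** m = 120 × 84 × 0.3 = 3,024.

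**Formula.** Var(log RR) = (1 − p1)/(m·π·p1) + (1 − p0)/(m·(1 − π)·p0), where p1 is the rate under intervention and p0 the rate under control. Power is from a noncentral F with 1 and n − 2 df and noncentrality (log RR)²/Var.

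**1. Printed inputs taken literally.** π = .25, p0 = .25, p1 = .3025.
- Var = .6975/(756 × .3025) + .75/(2,268 × .25) = .003050 + .001323 = .004373.
- log 1.21 = .1906; noncentrality = 8.31.
- Power = 81.6% (82.2% by normal approximation); 116 participants give 80%. This reproduces the claim.

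**2. Only the treatment probability changed.** π = .75, RR 1.21.
- Var = .001017 + .003968 = .004985; noncentrality = 7.29.
- Power = 76.4%; 132 needed for 80%.

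**3. Design probability, fall equal to the reciprocal.** π = .75, p0 = .25, RR = 1/1.21 = 0.826, p1 = .2066.
- Var = .7934/(2,268 × .2066) + .75/(756 × .25) = .001693 + .003968 = .005661; noncentrality = 6.42.
- Power = 71.0% (71.7% by normal approximation); 149 needed for 80%.
- With 162 retained (19% attrition): 83%. With 200: 90%.

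**4. Design probability, fall of 21%.** π = .75, p0 = .25, RR 0.79, p1 = .1975.
- Var = .001792 + .003968 = .005760; noncentrality = 9.65.
- Power = 86.9%; 100 needed for 80%.

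**5. Full relabelling.** .25 is the chance of control, 1.21 is control versus intervention, the rate is .25 under intervention and .3025 under control.
- The two variance terms are those of step 1 with the arms exchanged, so power is again 81.6%. The printed no-intervention rate of .25 is then wrong.

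**6. Effect detectable with 80% power** at n = 120, π = .75, p0 = .25: RR 0.807 (25% to 20.2%) gives 80.3%.

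**The case against.** The strongest reply is that this is a labelling slip. The design's control probability is exactly .25, and if 1.21 compares control with intervention, the calculation may already describe the 75/25 design and a fall. Step 5 confirms that this reading gives 81.6%. It is a plausible account, but it holds only if the printed no-intervention rate is replaced by .3025. With .25 kept, the reading becomes step 3, at 71%.

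Three further points stand.
- A reader might infer that the calculation was in fact run with 25% treatment and a rise in gambling. The match at 81.6% does not show this. The relabelled reading gives the same value, and RR 0.79 with π = .25 gives 81.5%.
- A reader might infer that each correction lowers power. That is so only while RR stays at 1.21. For a fall to 20.7%, moving from 25% to 75% treatment raises power from 65.7% to 71.0%.
- Sidedness is not stated. At a one-sided 5% level the reciprocal case reaches about 81% by normal approximation. The two-sided reading is the conventional one, but it is an assumption.

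Finally, the shortfall in step 3 is confined to the 40% attrition case, which the protocol itself calls conservative. At the 19% attrition also cited there, the same effect has 83% power.

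**Conclusion.** The point holds as a contradiction between the printed power inputs and the design. The arithmetic on the printed inputs is sound, but they do not describe a trial that treats 75% of eligible points and expects gambling to fall. Under the design with a no-intervention rate of .25, power at 120 is 71% for RR 0.826 and 87% for RR 0.79 (two-sided 5%, 84 decision points, availability 0.3, all next EMAs completed). Under those assumptions, no reading keeps every printed input and restores 80%.

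It would be tempting to conclude that the trial has 71% power and is underpowered. The documents do not support that, because no section states the size of the expected fall and 1/1.21 is only one candidate. What can be said is that sufficiency at 120 retained participants is not supported as printed, and that a reader cannot tell which effect the trial is able to detect.

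**What to change.** Rewrite the power statement in Sample Size:
- Rerun the same calculator with treatment probability .75 and a relative risk below 1 for intervention versus control.
- Name the reference condition for the randomization probability and for the relative risk, and state the no-intervention rate.
- Replace Cronbach α with the two-sided type I error rate; if a one-sided test was meant, say so.
- Restate the result for the effect actually intended. For example: with a no-intervention rate of .25, 120 participants give about 80% power for RR 0.807 (25% to 20.2%), 71% for RR 0.826 (1/1.21) and 87% for RR 0.79; for RR 0.826, 162 give 83% and 200 give 90%.
- If control was coded as the active level, correct the no-intervention rate to .3025 instead and keep the power figure.

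The cost is one paragraph and possibly a less favourable stated figure at 120 participants. Neither the design nor the recruitment target of 200 changes.
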